### Statistical Method

Data will be analyzed using the SPSS statistical program (SPSS Inc. Chicago, IL, USA). In order to compare the means of the quantitative variables when these followed a normal distribution, a variance analysis and Student's *t-*test will be used. For the rest of the variables, both the Mann-Whitney and Kruskal-Wallis tests will be performed. For categorical variables, a Chi-square test will be implemented. Results with a *P*-value lower than 0.05 will be considered statistically significant.

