Some published result must be interpreted with caution as the analysis is based on heterogeneous data with outcomes conditioned by the lack of an economical standardization of reported costs. A study from 2014 reported that robotic-assisted colorectal resections had higher total ($5,272 increase, *p* < 0.001) and direct costs ($4,432 increase, *p* < 0.001), longer operating time (39 min, *p* < 0.001), and were more frequently associated to postoperative bleeding (OR 1.6, *p* = 0.014) than laparoscopic resections. The data source for this study was a United States national inpatient database evaluating a total of 17,265 laparoscopic and 744 robotic colorectal resections between 2009 and 2011 (10). However, there were some limitations in this study that may have influenced the results. First, the authors used an administrative database which had the possibility of coding errors. Second, many centers were involved, which also suggests a high heterogeneity of the techniques in both the laparoscopic and robotic groups, including the type of devices, the implementation of hybrid vs. totally robotic techniques, the phase of the learning curve, and patient volume at the center. Furthermore, some data were missing, such as the conversion rate.

The main reasons why the costs of robotic approach are poorly reported in the literature are mainly due to the challenge in their calculation. If, from one hand, costs associated with the hardware are easy to obtain, the impact of the surgical procedure on overall costs is difficult to be quantified.

Indeed, overall costs should include not only operative costs but also costs related to the rehabilitation facility, days out of work after surgery and its impact on the quality of life (QoL), which make an exact estimate challenging. Studies which address the impact of costs of a new technique on QoL are named *cost-effectiveness studies*.

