### Study Population

Patients are considered eligible to enter the study if they meet the following inclusion criteria:

1. Adults aged ≥18 years of age.

2. Consecutive patients undergoing: distal pancreatectomy, gastrectomy (total and subtotal), sleeve gastrectomy, inguinal hernioplasty with mesh, rectal resection for cancer, Heller cardiomiotomy and Nissen procedure.

3. Type of disease approachable by both laparoscopic and robotic minimal access surgery.

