## Data Collection

### Clinical Data

Clinicians will be requested to register medical data related to surgery (operation equipment, skin-to-skin operating time, blood loss, surgical equipment, number of surgeons), hospital stay (intensive care unit, high dependency unit, ward), complications and associated management (interventions, additional imaging, additional hospitalization). This data will be entered into an electronic Case Report Form (eCRF) online database (CASTOR).

Complications will be classified according to the Clavien-Dindo classification of surgical complications (26) and registered as adverse or serious adverse events. Participants' overall morbidity will be assessed using the Comprehensive Complication Index (CCI) (27). The 95% confidence intervals (CI) for the difference in the means between the two groups will be reported as a primary result. Since the CCI is approximately normally distributed, the 95% CI can be computed using the normal distribution. Further descriptive measures will be reported in terms of mean and standard deviation.

Missing data will thus be managed depending on the cause of missingness. If missingness may directly or indirectly be related to the treatment, it may cause a bias even in the intention-to-treat analysis. In such a situation, the missing data will be reported in the final report, and missing data in the intention to treat analysis will be analyzed according to the worst-case scenario method (failure).

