## Sample Size Calculation and Statistical Methods

### Sample Size

There are concerns about calculating power and sample size in cost-effectiveness studies (28). Although there is some uncertainty, the Incremental Net Benefit (INB) is a measure that is easier to interpret and work with, since a positive INB means that the new proposed treatment is cost-effective (29). Medicare calculations of power and sample size are calculated against some value of Maximum Willingness to Pay (WTP) for a unit of treatment effect. The WTP is defined from a societal perspective, and, although in Spain there is no specific WTP threshold in healthcare, according to the National Institute for Health Care Excellence (NICE) (30) and Spanish Recommendations on Economic Evaluation of Health Technologies (31) we use a WTP of 20,000 € and 30,000 € per QALY as a threshold, to recognize which treatment is most cost-effective, as follow:

$$\begin{array}{l} \text{INB}=\left[\left(\text{EffectNew-EffectComparatore}\right)*\text{WTP}\right]\\ -\left(\text{CostNew-CostComparator}\right) \end{array}$$

This sample size calculation was realized with consultation of two statisticians.

Considering previous retrospective reports on cost-effectiveness studies (16–21) in which a minimum of 3,000 € for QALY gained was considered cost-effective, assuming a 5% lost-to-follow-up-rate and the two-sided significance level (α) set at 5% and power (1-β) at 80%, a minimum total of 60 patients need to be allocated in each procedure group comparison (30 laparoscopic vs. 30 robotic).

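### Student's t-test is named for comparing means although nothing stated keeps the arms equal in size; naming Welch's test would protect the secondary P values at negligible cost

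*Protocol article*

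**What the plan says.** The Statistical Method section states that, to "compare the means of the quantitative variables when these followed a normal distribution, a variance analysis and Student's" t-test will be used. Variables not treated as normal go to rank tests: "For the rest of the variables, both the Mann-Whitney and Kruskal-Wallis tests will be performed". A P "value lower than 0.05 will be considered statistically significant". The software is SPSS. The section mentions neither pooled nor unequal-variance forms.

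Three other places bear on arm sizes. Study Design describes an observational study. Study Population enrols by procedure: "Consecutive patients undergoing: distal pancreatectomy, gastrectomy (total and subtotal), sleeve gastrectomy, inguinal hernioplasty with mesh", and further procedures. Sample Size asks for "a minimum total of 60 patients need to be allocated in each procedure group comparison (30 laparoscopic vs. 30 robotic"), which is a floor. The article states no cap, matching or fixed ratio.

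For the Comprehensive Complication Index, the Clinical Data section calls the 95% interval for the mean difference a primary result and adds: "Since the CCI is approximately normally distributed, the 95% CI can be computed using the normal distribution". It does not say how the standard error is formed.

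**The concern.** Student's t-test and ordinary analysis of variance estimate one common variance from all arms. With equal arm sizes this is almost harmless even when the spreads differ. With unequal sizes the larger arm dominates the pooled variance. If the smaller arm is the more variable, the standard error is too small and differences are called significant too often. If the larger arm is the more variable, the standard error is too large and real differences are missed.

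In a randomised 1:1 trial the allocation would largely remove the issue. Here the arms follow local practice, and whichever approach is commoner can continue to accrue once both have reached 30. The Methods for Minimizing Bias section also stratifies by surgeon experience, hospital type and number of beds, so a procedure with 30 per arm overall need not have equal arms within strata.

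At stake are the P values for normally treated variables among the secondary efficacy and safety comparisons. These include any t-test on the Comprehensive Complication Index, since the protocol declares it approximately normal.

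**Working it through.** **The plan's own figure.** Sample Size gives 30 per arm, 5% loss, two-sided 5% and 80% power. No SD is given, so 60 cannot be reproduced, only solved backwards. Evaluable per arm: 30 × 0.95 = 28.5. Implied standardised difference: (1.960 + 0.842) × √(2/28.5) = 0.74. This says nothing about how the spreads of the two arms compare.

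**Inputs for the check.** From the protocol: Student's t-test, P < 0.05, minimum 30 versus 30. Assumed, because the protocol does not give them: arm sizes from 30:30 to 90:30, SD ratios from 1 to 3, normal data.

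**Formulas.** Let n₁ and σ₁ be the size and SD of the larger arm, n₂ and σ₂ those of the smaller.
- Pooled variance (expected): s² = [(n₁ − 1)σ₁² + (n₂ − 1)σ₂²] / (n₁ + n₂ − 2)
- Pooled SE² = s²(1/n₁ + 1/n₂)
- True SE² = σ₁²/n₁ + σ₂²/n₂
- Approximate type I error = 2[1 − Φ(t × pooled SE / true SE)], with t the critical value on n₁ + n₂ − 2 degrees of freedom

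**30:30.** Pooled SE² = (σ₁² + σ₂²)/30 = true SE². The ratio is exactly 1 whatever the SDs.

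**60:30, smaller arm 1.5 times as variable.** s² = (59 × 1 + 29 × 2.25)/88 = 1.412. Pooled SE² = 1.412 × 0.05 = 0.0706. True SE² = 1/60 + 2.25/30 = 0.0917. Ratio of SEs = √(0.0706/0.0917) = 0.878. Approximate error: 1.987 × 0.878 = 1.744, giving 8.1%.

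**60:30, larger arm 1.5 times as variable.** s² = (59 × 2.25 + 29 × 1)/88 = 1.838. Pooled SE² = 0.0919. True SE² = 2.25/60 + 1/30 = 0.0708. Ratio = 1.139. Approximate error: 1.987 × 1.139 = 2.264, giving 2.4%.

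**40:30, SD ratio 1.5.** The same steps give SE ratios of 0.946 (smaller arm wider, about 5.9%) and 1.057 (larger arm wider, about 3.5%).

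These approximations treat the pooled SE as fixed. Simulation lets it vary (200,000 data sets per scenario, true difference zero):

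| Arm sizes | SD ratio | Student, smaller arm wider | Student, larger arm wider |
|---|---|---|---|
| 30:30 | 1.5 | 5.1% | 5.1% |
| 30:30 | 3 | 5.3% | 5.3% |
| 40:30 | 1.5 | 6.4% | 3.8% |
| 60:30 | 1.5 | 8.5–8.6% | 2.6% |
| 60:30 | 2 | 11.1% | 1.8% |
| 90:30 | 2 | 15.3% | 0.8% |

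With equal SDs, Student's test stayed at 4.9–5.1% at every arm ratio. Welch's test stayed at 4.9–5.1% in every scenario.

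**Power.** At 60:30 with the larger arm 1.5 times as variable, a difference that Welch's test detects with about 80% power is detected by Student's test with about 72%.

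**Intervals.** If the normal interval for the Comprehensive Complication Index uses an unpooled standard error, it misses the truth 5.2–6.0% of the time over arm sizes 30:30 to 120:30 and SD ratios 1 to 3, close to nominal.

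**The case against.** The strongest reply is that a condensed article naming Student's t-test has not committed itself to pooling. The variance form may be settled in a fuller document, and the planned software can produce the unequal-variance result. Part of this stands: pooling is inferred from the name of the test. But the name is what the text fixes, and an analysis plan written to that text would naturally carry it forward.

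The reply also notes that the harm needs unequal size and unequal spread together, and that the protocol documents neither. This stands. At the only sizes stated the error is at most 0.3 percentage points, and the larger errors in the table come from assumed ratios.

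Three stronger readings are tempting and not supported:

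- **That the planned 95% intervals are wrong.** No interval in the article is tied to the t-test. The complication index interval uses the normal distribution, with pooling unstated. The economic intervals are simulation percentiles (Sensitivity Analysis).
- **That the arms will be grossly unequal.** Current Evidence cites a United States database with "a total of 17,265 laparoscopic and 744 robotic colorectal resections between 2009 and 2011", about 23 to 1 (17,265/744 = 23.2). Those older administrative data, whose limitations the article itself lists, do not predict arm ratios in Spanish centres in 2022.
- **That differing surgeon experience makes the spreads unequal.** The protocol records and stratifies on experience but gives no data on variability.

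The scope is also narrow, because variables that are not normal go to rank tests.

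**Conclusion.** The point holds as a minor improvement. The named test relies on equal variances, and nothing stated in the design secures the equal arm sizes that would make that reliance harmless. Under the assumed SD ratio of 1.5, moderate imbalance moves a nominal 5% test to between 2.6% and about 8.5%. The direction depends on which arm is the more variable, so the test cannot be defended as conservative. If the arms finish close to 30:30, or the spreads are equal, there is practically no error.

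A reader might infer that the cost-effectiveness conclusion is at risk. It is not: the primary aim is answered through the ICER, INB, Monte Carlo simulation and acceptability curve, none of which uses this test. The complication index difference, although labelled a primary result in Clinical Data, is to be reported by its interval. What remains open there is only that its standard error is unspecified, so its interval and any accompanying P value could rest on different standard errors.

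**What to change.** In Statistical Method, name Welch's unequal-variance t-test and Welch's analysis of variance as the default for every comparison of means, and state that no preliminary test of variances will decide the choice. In Clinical Data, state that the interval for the complication index mean difference uses the same unpooled standard error. This takes about one sentence in each section. It needs no further patients or data, the planned software can produce it, and the loss of power is negligible if sizes and variances turn out equal.

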### Cost-Effectiveness Analysis

The economic evaluation will be performed as cost effectiveness and cost–utility analyses from a healthcare perspective, with a time horizon of 3 months.

The cost–utility endpoint will be the cost per QALY. The results will be reported in accordance with CHEERS guidelines (23). Data will be collected in the early post-operative period of time (3 months from the surgery) in order to capture as much as possible only the QoL mainly related to the surgical approach instead of the issues related to all treatment process (adjuvant treatment, stoma issues, etc.) which patients are dealing with in a later period of time.

An independent company (Institute for Validation of Clinical Efficacy - IVEC) will perform the financial analysis, eliminating the risk of an observer bias.

A model-based cost-utility analysis estimating mean costs and QALYs per patient will be performed. A stochastic cost-utility analysis will be undertaken. The incremental cost-effectiveness ratio (ICER) will be estimated using the overall costs of the robotic and laparoscopic procedures and QALYs derived from patient interviews to find the incremental cost per QALYs gained.

The INB will be calculated to estimate decision-makers maximum willingness to pay (WTP) for a QALY gained. The INB will be calculated as the mean QALYs per patient multiplied by WTP threshold minus the mean cost per patient for the treatment. The decision rule is to adopt the treatment if the INB > 0, and the alternative with the highest INB represents best value for money.

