### Acceptability Curve

The analysis will also include a cost-effectiveness acceptability curve that plots the probability that the robotic technique is cost-effective relative to laparoscopy over a reasonable range of levels of WTP.

Although there is no specific willingness to pay threshold in healthcare in Spain, as described above, according to the National Institute for Health Care Excellence (NICE) (30) and the Spanish Recommendations on Economic Evaluation of Health Technologies (31) a WTP of 20,000 € and 30,000 € per QALY will be used as a threshold to recognize which treatment is most cost-effective.

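### The Cost-Effectiveness Analysis section gives the name INB to a single arm's net monetary benefit, yet applies a greater-than-zero adoption rule that is valid only for the difference between arms

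*Protocol article*

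**What the plan says.** The protocol article defines the incremental net benefit (INB) twice.

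- **Sample Size section.** A displayed formula takes the new treatment's effect minus the comparator's effect, multiplies by WTP, and subtracts the new treatment's cost minus the comparator's cost. The text explains that "a positive INB means that the new proposed treatment is cost-effective". This is an increment between two treatments.
- **Cost-Effectiveness Analysis section.** "The INB will be calculated as the mean QALYs per patient multiplied by WTP threshold minus the mean cost per patient for the treatment". No comparator appears.

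The second definition is followed at once by the rule: "The decision rule is to adopt the treatment if the INB > 0, and the alternative with the highest INB represents best value for money".

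Two further statements set the scale. The evaluation is run "with a time horizon of 3 months", and the Sample Size section says "we use a WTP of 20,000 € and 30,000 € per QALY as a threshold". The Acceptability Curve section repeats the same two values.

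**The concern.** One name covers two different quantities. The second is the net monetary benefit of a single arm. It is not loose shorthand for a difference, because the rule goes on to compare INB values across alternatives, which presumes one value per arm.

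Zero is a natural cut-off for the increment: above zero, the new treatment is worth its extra cost at the chosen WTP. For a single arm, the sign says only whether three months of that patient's quality-adjusted life, priced at the WTP, exceeds the cost of the operation. That does not compare robotic with laparoscopic surgery.

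This is the only sentence in the article labelled as a decision rule, and the section hands the financial analysis to an independent company. A company that follows the sentence literally could report both approaches, or neither, as adoptable for a given procedure.

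**Working it through.** **Plan's own figure.** The article reports no numerical INB, so there is none to reproduce. The check is algebra plus a ceiling derived from the stated inputs.

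**Inputs from the article.** Time horizon 3 months (Cost-Effectiveness Analysis). WTP 20,000 and 30,000 EUR per QALY (Sample Size; Acceptability Curve).

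**Assumption.** Utility is at most 1.

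**Step 1: the two definitions.** Write NMB for the per-arm quantity, R for robotic and L for laparoscopic.

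- Cost-Effectiveness Analysis: NMB = QALY × WTP − cost, one value per arm.
- Sample Size: INB = (QALY_R − QALY_L) × WTP − (cost_R − cost_L).
- Hence INB = NMB_R − NMB_L.

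Choosing the arm with the higher NMB is therefore the same as reading the sign of the true INB. Asking whether each NMB exceeds zero is not. That question separates the arms only when one value is above zero and the other is not. When both lie on the same side of zero, it returns adopt both or adopt neither.

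**Step 2: the ceiling.** Maximum QALYs per arm = 1 × 3/12 = 0.25.

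- At WTP 20,000: 0.25 × 20,000 = 5,000 EUR.
- At WTP 30,000: 0.25 × 30,000 = 7,500 EUR.

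If both arms of a procedure cost more than 7,500 EUR on average, both values are negative at both WTP levels, even if robotic surgery is cheaper and better. If each arm costs less than its own QALY value, both are positive, even if one arm is dominated.

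**Step 3: illustrations.** The QALYs and costs below are assumed, because the article gives none.

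*(a) Low-cost procedure.* QALYs 0.205 (R) and 0.200 (L); costs 3,000 and 2,000 EUR.

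| | WTP 20,000 | WTP 30,000 |
|---|---|---|
| NMB_R | 4,100 − 3,000 = +1,100 | 6,150 − 3,000 = +3,150 |
| NMB_L | 4,000 − 2,000 = +2,000 | 6,000 − 2,000 = +4,000 |
| INB | 100 − 1,000 = −900 | 150 − 1,000 = −850 |

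The zero cut-off adopts both arms. The true INB says robotic is not cost-effective. The highest-value clause picks laparoscopic, in agreement with the true INB.

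*(b) High-cost procedure.* QALYs 0.220 (R) and 0.200 (L); costs 9,200 and 9,000 EUR.

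| | WTP 20,000 | WTP 30,000 |
|---|---|---|
| NMB_R | 4,400 − 9,200 = −4,800 | 6,600 − 9,200 = −2,600 |
| NMB_L | 4,000 − 9,000 = −5,000 | 6,000 − 9,000 = −3,000 |
| INB | 400 − 200 = +200 | 600 − 200 = +400 |

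The zero cut-off rejects both arms. The true INB says robotic is cost-effective. The highest-value clause picks robotic, again in agreement.

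**The case against.** The best defence is that the article already holds the right formula. It is displayed in the Sample Size section, and the word incremental is part of the term. The surrounding analysis is comparative: the primary aim is the extra cost per QALY gained, the ICER uses the costs and QALYs of both procedures, and the acceptability curve gives the probability that robotic is cost-effective relative to laparoscopy. The second half of the decision sentence also selects the correct arm when it is applied to per-arm values. An analyst who reads the whole document could reach the right answer.

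Most of this stands, and it limits the consequence. It does not remove the conflict: the article states two formulas under one name, and the two halves of one sentence can give different answers with nothing to say which governs.

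A reader might infer more, namely that the study would reach an arbitrary verdict whatever the comparison shows. The documents do not support that, because only the greater-than-zero clause fails.

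A reader might also see a further error in the use of two thresholds ("a WTP of 20,000 € and 30,000 € per QALY will be used as a threshold"). That does not follow either. Reporting at both values is acceptable, and the planned curve shows how the conclusion depends on WTP.

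**Conclusion.** The point holds as an inconsistent definition with a misapplied cut-off. The Cost-Effectiveness Analysis section contradicts the Sample Size formula, and "The decision rule is to adopt the treatment if the INB > 0" is valid only for the increment.

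The possible size of the problem follows from the stated horizon and thresholds: an arm's QALYs are worth at most 5,000 or 7,500 EUR, given utility no higher than 1 and QALYs counted over the three months. Whether any included procedure falls in the reject-both or adopt-both range cannot be settled from the article, since it gives no costs or utilities.

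The ICER, the acceptability curve and the sample size are unaffected. The wording should be corrected before the economic analysis is run.

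**What to change.** In the Cost-Effectiveness Analysis section:

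1. Replace the INB sentence with the Sample Size formula, naming the arms: INB = WTP × (QALY robotic − QALY laparoscopic) − (cost robotic − cost laparoscopic).
2. Call the per-arm quantity, WTP × mean QALYs − mean cost, the net monetary benefit.
3. Apply the greater-than-zero rule only to the INB so defined: robotic is cost-effective at the given WTP if INB > 0.
4. Use the highest-value rule only for the per-arm net monetary benefit, where it gives the same choice.

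The cost is a few sentences of wording. No new data, no change to the sample size and no additional analysis are needed.
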